#### 6.2.4 Raltegravir containing arm

Raltegravir does not inhibit CYP1A2, CYP2B6, CYP2C8, CYP2C9, CYP2C19, CYP2D6 nor CYP3A4 in vitro. Moreover, in vitro, raltegravir does not induce CYP3A4. A midazolam drug interaction study confirmed the low propensity of raltegravir to alter the pharmacokinetics of agents metabolised by CYP3A4 in vivo by demonstrating a lack of effect of raltegravir on the pharmacokinetics of midazolam, a sensitive CYP3A4 substrate. Similarly, raltegravir is not an inhibitor of the UDP-glucuronyltransferases (UGT) tested (UGT1A1, UGT2B7), and raltegravir does not inhibit P-glycoprotein-mediated transport. Based on these data, raltegravir is not expected to affect the pharmacokinetics of drugs that are substrates of these enzymes or of

P-glycoprotein (e.g., protease inhibitors, NNRTIs, methadone, opioid analgesics, statins, azole antifungals, proton pump inhibitors, oral contraceptives, and anti-erectile dysfunction agents). In drug interaction studies, raltegravir did not have clinically meaningful effects on the pharmacokinetics of lamivudine nor tenofovir.

Caution should be used when co-administering raltegravir with strong inducers of uridine diphosphate glucuronyltransferase (UGT)1A1 (e.g. rifampin) due to reduced plasma concentrations of raltegravir. The impact of other inducers of drug metabolising enzymes, such as phenytoin and phenobarbital, on UGT1A1 is unknown. Other less strong inducers (e.g., efavirenz, nevirapin, rifabutin, St-John's wort) may be used with the recommended dose of raltegravir.

In healthy subjects, co-administration of raltegravir with omeprazole increases raltegravir plasma levels. As the effects of increasing gastric pH on the absorption of raltegravir in HIV-infected patients are uncertain, use raltegravir with medicinal products that increase gastric pH (e.g. proton pump inhibitors and H2 antagonists) only if unavoidable (see SmPC of Isentress®).

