| STUDY DRUGS                 | 
Group 1: darunavir/r QD + tenofovir/emtricitabine QD (fixed dose combination)
 
Group 2: darunavir/r QD + raltegravir BID
                                                                                                                                                                                                                                                                                                                                                                                                                                                                                                                                                                                                                                                                                                                                                                                                                                                                                                                                                                                                                                                                                                                                                                                                                                                                                                                                                                                                                                                                                                                                                                                                                                                                                                                                                                                                                                                                                                                                                                                                                                                              |

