### 6.2.3 Darunavir/ritonavir containing arms

Darunavir and ritonavir are both inhibitors of CYP3A. Co-administration of darunavir/ritonavir with drugs primarily metabolised by CYP3A may result in increased plasma concentration of such drugs, which could increase or prolong their hepatic effect and adverse events (see SmPC of Prezista® and Norvir®).

Drugs that should not be co-administered with darunavir/ritonavir:

- $\alpha_1$ -adrenoreceptor antagonist: alfuzosin  
Darunavir/ritonavir should not be used in combination with alfuzosin since this may cause increased plasma concentrations of alfuzosin which may lead to severe hypotension
- Analgesics: pethidine, piroxicam, propoxyphene  
Darunavir/ritonavir should not be used in combination with pethidine, piroxicam or propoxyphene, as this may cause increased plasma concentrations of these analgesics and thereby increases the risk of serious respiratory depression or haematologic abnormalities, or other serious adverse effects from these agents.
- Antiarrhythmics: amiodarone, bepridil, encainide, flecainide, propafenone, lidocaine (systemic), quinidine  
Concentrations of these agents may be increased when co-administered with darunavir/ritonavir, thereby, increasing the risk of arrhythmias or other serious adverse effects from these agents.
- Antibiotics: fusidic acid  
Co-administration with darunavir/ritonavir can result in increased plasma concentrations of fusidic acid and ritonavir.
- Anticonvulsant drugs: phenobarbital, phenytoine  
Phenobarbital and phenytoine are inducers of CYP450 enzymes. Darunavir/ritonavir should not be used in combination with phenobarbital or phenytoine as coadministration may cause significant decreases in darunavir plasma concentrations. This may result in loss of therapeutic effects of darunavir.
- Antihistamines: astemizole, terfenadine.  
Contraindicated due to potential for serious and/or life-threatening reactions such as cardiac arrhythmias.
- Antimycobacterial: rifampicin.

Rifampicin is an inducer of CYP450 metabolism. Darunavir/ritonavir should not be used in combination with rifampicin, as this may cause significant decreases in darunavir plasma concentrations. This may result in loss of therapeutic effects of darunavir.

- Ergot derivatives: dihydroergotamine, ergonovine, ergotamine, methylergonovine  

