Contraindicated due to potential for serious and/or life-threatening reactions such as acute ergot toxicity characterised by peripheral vasospasm and ischemia of the extremities and other tissues.
- Gastrointestinal motility agent: cisapride  
Contraindicated due to potential for serious and/or life-threatening reactions such as cardiac arrhythmias.
- HMG-CoA reductase inhibitors: simvastatine, lovastatine  
Potential for serious reactions such as risk of myopathy including rhabdomyolysis.
- Herbal products: St.-John's wort and Hypericum perforatum-containing products  
Coadministration with darunavir/ritonavir can cause significant decreases in darunavir/ritonavir concentrations. This may result in loss of therapeutic effect of darunavir.
- Neuroleptics/anti-psychotics: pimozide, clozapine, sertindole  
Contraindicated due to increased plasma concentrations of clozapine, pimozide and sertindole, and potential for serious and/or life-threatening reactions such as cardiac arrhythmias
- Oral contraceptives/oestrogen: ethynil estradiol, norethindrone.  
Plasma concentrations of ethynil estradiol may be decreased due to induction of its metabolism by ritonavir. Mechanical contraception + a second method other than an oral contraceptive should therefore be used during the trial. However, if there is a medical reason for a woman to use oral contraceptives during the trial in addition to mechanical contraception + a second method other than an oral contraceptive, this is not a formal contraindication.
- PDE-5 inhibitor: sildenafil  
Sildenafil is contraindicated only when used for the treatment of pulmonary arterial hypertension, given the increased risk for sildenafil-associated adverse events such as hypotension and syncope. In patients with erectile dysfunction, sildenafil should be used with caution (see below).
- Sedative/hypnotics: Clorazepate, diazepam, estazolam, flurazepam, oral midazolam, pethidine, and triazolam  
Contraindicated due to potential for serious and/or life-threatening reactions such as prolonged or increased sedation or respiratory depression.

Other potentially significant drug interactions:

Alterations in dose or regimen may be recommended.

- Analgesics: buprenorphine, fentanyl, methadone, morphine  
The clinical relevance of the increase in norbuprenorphine pharmacokinetic parameters has not been established. Dose adjustment for buprenorphine may not

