Darunavir/ritonavir can be administered with H2-receptor antagonists and proton pump inhibitors without any dose adjustments.
- **HMG-CoA reductase inhibitors: atorvastatin, pravastatin, rosuvastatin**  
When atorvastatin or rosuvastatin and darunavir/ritonavir are co-administered, it is recommended to start with the lowest possible dose of atorvastatin or rosuvastatin with careful monitoring. When pravastatin and darunavir/ritonavir are co-administered, the mean increase in pravastatin AUC is 81 %. However, pravastatin AUC increases by up to 5-fold in some subjects. The mechanism of this interaction is unknown. It is recommended to start with the lowest possible dose of pravastatin.
- **Immunosuppressants: ciclosporin, everolimus, tacrolimus, sirolimus**  
Plasma concentrations of ciclosporin, everolimus, tacrolimus or sirolimus may be increased when co-administered with darunavir/ritonavir. Therapeutic concentration monitoring of the immunosuppressive agent is recommended
- **PDE-5 inhibitors: sildenafil, vardenafil, tadalafil**  
Concomitant use of PDE-5 inhibitors for treatment of erectile dysfunction should be done with caution. If required, recommended dosage is:
  - sildenafil: ≤ 25 mg /48 hours
  - vardenafil: ≤ 2,5 mg /72 hours
  - tadalafil: ≤ 10 mg /72 hoursConcomitant use of darunavir/ritonavir and sildenafil is contraindicated in pulmonary arterial hypertension.
- **Sedative/hypnotics: alprazolam, buspirone, parenteral midazolam**  
Alprazolam metabolism is inhibited following the introduction of ritonavir. After ritonavir use for 10 days, no inhibitory effect of ritonavir has been observed. Caution

is warranted during the first several days when alprazolam is co-administered with ritonavir, before induction of alprazolam metabolism develops.

Caution should be used with co-administration of darunavir/ritonavir and parenteral midazolam. Data from concomitant use of parenteral midazolam with other protease inhibitors suggest a possible 3 – 4 fold increase in midazolam plasma levels. If darunavir/ritonavir is co-administered with parenteral midazolam, it should be done in an intensive care unit (ICU) or similar setting which ensures close clinical monitoring and appropriate medical management in case of respiratory depression and/or prolonged sedation. Dosage adjustment for midazolam should be considered, especially if more than a single dose of midazolam is administered.

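### For the raltegravir arm, Sections 6.2.3 and 6.2.4 contradict each other on St John's wort and differ in strength on rifampicin

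*Protocol*

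**What the plan says.** The Summary gives the experimental regimen as "Group 2: darunavir/r QD + raltegravir BID", and protocol Section 5.2.2 confirms that all its components run from W00 to the end of follow-up. No patient is allocated raltegravir without darunavir/ritonavir.

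Co-medication is set out by component. The heading "6.2.3 Darunavir/ritonavir containing arms" is plural and so takes in both arms. Its first list is introduced by "Drugs that should not be co-administered with darunavir/ritonavir". Two entries matter here:

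- "Herbal products: St.-John's wort and Hypericum perforatum-containing products", with a warning that darunavir may lose its therapeutic effect.
- Rifampicin: "Darunavir/ritonavir should not be used in combination with rifampicin, as this may cause significant decreases in darunavir plasma concentrations", followed by the same kind of warning.

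Section 6.2.4 is headed for the raltegravir arm. On strong inducers it says "Caution should be used when co-administering raltegravir with strong inducers of uridine diphosphate glucuronyltransferase" 1A1, naming rifampin (the same drug as rifampicin) as its example. On weaker ones it says "Other less strong inducers (e.g., efavirenz, nevirapin, rifabutin, St-John's wort) may be used with the recommended dose of raltegravir". The only source it points to is the raltegravir product information. It does not mention Section 6.2.3.

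**The concern.** An investigator with a raltegravir-arm patient would naturally look at the section headed for that arm. On St John's wort that section gives permission, while the preceding section prohibits it for the same patient. On rifampicin it gives a caution where the preceding section gives a prohibition. The protocol's own stated reason for the stricter text is loss of darunavir effect, so this is a safety instruction and not background pharmacology.

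The situation is foreseeable for rifampicin. Section 4.3 excludes mycobacteriosis under treatment, but only at entry. Appendix 4 lists tuberculosis at any site as a Category C event, which can arise during follow-up. Section 7.12 makes the need for a medication incompatible with the study drugs a ground for considering regimen termination. Under Section 3.2, discontinuation for any reason is a secondary endpoint and also counts towards loss of virologic response. Two sites reading different sections could therefore handle the same event differently. The ambiguity exists in one arm only of an open-label trial.

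**Working it through.** No arithmetic applies. The check sets the two sections side by side, product by product, for a patient taking darunavir/ritonavir and raltegravir together. It asks whether both statements can be followed.

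| Product | Section 6.2.3 (darunavir/ritonavir) | Section 6.2.4 (raltegravir) | Result |
|---|---|---|---|
| St John's wort | On the list of drugs not to be co-administered | May be used | Contradiction |
| Rifampicin / rifampin | On the same list | Caution | Mismatch in strength |
| Phenytoin, phenobarbital | On the same list | Effect on UGT1A1 unknown; no permission given | No conflict |
| Rifabutin | Allowed, with an adjusted rifabutin dose | Allowed, with the recommended raltegravir dose | Compatible |
| Efavirenz, nevirapine | Not listed | May be used | No conflict between the two sections |
| H2 antagonists, proton pump inhibitors | Allowed: "proton pump inhibitors without any dose adjustments" | Only where unavoidable | Both can be followed |

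The reasoning for the rows that need it:

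1. **St John's wort.** Taken at face value, one section forbids what the other permits for the same patient. The two agree only if the permission in 6.2.4 is read as limited to the raltegravir component. The text does not state that limit, and the section heading names the arm, not the drug.
2. **Rifampicin.** Caution and prohibition are not logically exclusive, because a prohibition satisfies any caution. But a reader who sees only 6.2.4 would take it that use with care is acceptable, which 6.2.3 does not allow.
3. **Acid reducers.** The 6.2.3 statement concerns darunavir/ritonavir; the 6.2.4 statement adds a restriction for raltegravir. A site can comply with both.
4. **Phenytoin and phenobarbital.** A statement that an effect is unknown does not lift a prohibition made elsewhere.

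Of the six rows, one is a contradiction, one is a mismatch in strength, and four are consistent.

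**The case against.** The strongest reply is that the two sections are cumulative. Section 6.2.3 covers every arm containing darunavir/ritonavir, its prohibitions are explicit, and nothing in 6.2.4 lifts them. Section 6.2.4 can then be read as interaction information on one component: no change to the raltegravir dose is needed with weaker inducers. On that reading a careful investigator reaches a single answer.

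Much of this stands. A reader might infer that permitted co-medication in the raltegravir arm is undefined, and the documents do not support that, because 6.2.3 expressly reaches that arm. A reader might also infer a general conflict over enzyme inducers and acid reducers; the comparison shows it is confined to two products. Entry restrictions help as well: Section 4.3 excludes contraindicated concomitant treatment and mycobacteriosis under treatment.

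What does not stand is the conclusion that nothing needs changing. The cumulative reading is an inference that the protocol never states. Section 6.2.4 comes later, is specific to the arm, and has neither a cross-reference nor a rule of precedence. Its permission is worded for raltegravir taken without regard to darunavir/ritonavir, a situation that the randomised regimen does not contain.

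**Conclusion.** The point holds in narrow form: a direct contradiction on St John's wort and a mismatch in strength on rifampicin, both in an operative section on medications that are not permitted. It should be corrected because it bears on patient safety and on regimen-termination decisions.

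Its statistical size cannot be given. A reader might infer a bias in the primary comparison, but the documents report no frequency of use for either product. With the planned 400 patients per arm, one additional failure would move that arm's crude proportion by 1/400 = 0.25 percentage points, against a margin of 9. That is arithmetic on a single hypothetical patient, not an estimate of effect. Extra failures in the raltegravir arm would also count against non-inferiority and would not produce a false claim of it. No endpoint definition, margin or analysis rule in Section 9 depends on this text.

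Section 9.1 records that enrolment was complete at the time of amendment 5.0. The live question is therefore management during treatment, not eligibility. The conclusion assumes only that sites work from the protocol text as written.

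**What to change.** Reconcile Sections 6.2.3 and 6.2.4 for the combination that raltegravir-arm patients actually take. This can be a single list for that regimen, or a sentence in 6.2.4 stating which section governs for St John's wort and rifampicin where the two differ. Using one name for rifampicin throughout would also help. Which clinical rule should apply is for the sponsor and its clinical advisers to settle; no view is taken here.

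The other products in the comparison need no correction, although a general cross-reference from 6.2.4 to 6.2.3 would do no harm.

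The cost is a change of protocol wording, handled under the amendment procedure in Section 11.3, and a notice to sites. Sample size, endpoints, visit schedule and analysis are unaffected.

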### **6.3 Data on concomitant medication**

For all concomitant medications the following data need to be recorded:  
commercial name of the product, formulation, dosage per drug unit, prescribed dosage, indication, start date and stop date.

## 7. STUDY CONDUCT

### 7.1 Signature of informed consent

Written informed consent must be obtained prior to the initiation of any study related intervention.

The investigating physician informs the patient of the objectives, type of constraints and foreseeable risks of the study. The investigator is responsible for ensuring that the subject fully understands the nature and purpose of the study. Information should be given in both oral and written form. No subject should be obliged to participate in the study. Subjects must be given ample opportunity to enquire about details of the study. The information must make clear that refusal to participate or withdrawal from the study at any stage is without any prejudice to the subject's subsequent care. Women should be informed about possible risks in case of pregnancy and advised not to become pregnant during the trial.

Subjects must be allowed sufficient time to decide whether or not they wish to participate.

The subject must be made aware of (and give consent to) the fact that monitors, auditors, and representatives of Independent Ethic Committees and regulatory authorities are granted direct access to the subjects medical records without violating subject confidentiality, and to the extent permitted by applicable regulations. The subject should be informed that by signing the informed consent form, the subject authorises such access.

The patient must be informed that biological samples taken within the framework of the study are anonymised and stored at a central location. Sample may be shipped from one country to another for storage and analysis. These samples are to be used for the scientific objectives described in this protocol or for future studies for which a separate information and consent form has to be signed off by the patients, excluding any commercial exploitation.

The patient signs and dates the informed consent. The informed consent is dated and countersigned by the investigator or a delegated person who explained the trial. The investigator or his delegate also inscribes his complete address and telephone number on the consent form. The number of informed consent signed depends on national recommendations. A copy of the signed informed consent is given to the patient.

Signed informed consents are retained by the investigator and made available (for review only) to the study monitor, auditor and inspector, upon request. An anonymised copy of the signed consent form is provided to the sponsor or its delegate.

### 7.2 Screening visit (W-6 to W-1)

A screening assessment for eligibility is performed between week -6 and week -1.

If patients with acute opportunistic infections are screened, the screening period should not exceed 2 weeks (screening visit between week -2 and week -1).

Signed and written informed consent for the trial must be obtained at latest at the screening visit and prior to the initiation of any study related intervention.

Screening procedures include:

- demographic information: date of birth, sex, ethnic group, country of birth
- history of HIV-associated conditions: mode of infection, CD4 nadir, date of first positive HIV-1 test, date of last HIV-1 negative test (if known), CDC stage
- documentation of historical genotype testing results, if available
- relevant medical history
- current medical conditions
- current medication
- recording of contraceptive methods in women
- assessment of inclusion and non-inclusion criteria
- complete physical examination including height and body weight (nude or light clothing only), heart rate and blood pressure
- blood sample for local laboratory assessments

laboratory assessments:

- plasma HIV-1 RNA
- HIV-1 genotypic resistance profile (if not previously available. Original test results of previous genotypic resistance profile must be available)
- HIV-1 subtype (if not previously available)
- CD4+ (mandatory even if  $CD4 \leq 500/mm^3$  on a sample taken within 3 months before screening)
- hepatitis serology: HBs Ag; HCV antibodies (if not previously available or if last assessment > 12 months before screening and HCV Ab negative, HBs Ab and HBc Ab negative)
- haematology: complete blood count, platelets; clinical chemistry: creatinine, alkaline phosphatase, ALAT, ASAT, albumin
- coagulation: prothrombin time (INR)
- pregnancy test (serum beta-HCG) in all women of child bearing potential
- estimation of glomerular filtration rate (see Cockcroft & Gault equation in appendix 7)

### 7.3 Randomisation and treatment allocation

Staff from the clinical site sends a randomisation request to the responsible regional CTU when results of screening assessment are available and at the latest 7 days prior to W00.

Results of genotypic testing should be available before randomisation. However, if the patient presents with an acute opportunistic infection requiring urgent initiation of antiretroviral therapy, the patient may be enrolled and start trial treatment even if the results

of the genotype are still pending. In this case, conditions of one of the following two scenarios must be fulfilled, to enrol the patient in the trial:

- The patient has an acute opportunistic infection requiring urgent initiation of antiretroviral therapy (as judged by the investigator) and there is no evidence of any major IAS-USA mutation conferring resistance to one or more of reverse transcriptase or protease inhibitors on a historical genotype.
- The patient has an acute opportunistic infection requiring urgent initiation of antiretroviral therapy (as judged by the investigator), there is no historical genotype and screening genotyping is underway, but results are not yet available.

If urgent treatment initiation is required, the regional CTU should be contacted to arrange randomisation within due time.

The randomisation of patients is performed by the regional CTU after verification of the eligibility criteria. A centralised web-based computer program that guarantees process safety and traceability is used for randomisation. A written SOP describes the randomisation process.

Patients meeting the eligibility criteria are randomly allocated in a 1:1 ratio at trial entry to start one of the following open-label regimens over at least 96 weeks: darunavir/r + tenofovir/emtricitabine or darunavir/r + raltegravir.

Randomisation is centralised and stratified according to the following factors:

- Country
- participation in the "Viral and immunologic dynamics and inflammation sub-study"

The randomisation list is established by the study statistician prior to the start of the study.

